### Statistical analysis

#### Sample size

On the basis of the literature [37,38] group visits may be expected to lead to a clinically relevant improvement in quality of life of 5 points on the total SF-36 score. Assuming a standard deviation of 12 [39], 92 patients need to be enrolled in both groups to achieve a statistical power of 80% (alpha = 0.05, two-sided). Taking into account non-evaluable patients, to adjust for imbalances and to be able to do subgroup analysis on age, sex, gender and severity, 135 patients will be enrolled in both groups. In order to be able to evaluate 270 patients, the aim is to include 300 patients.

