#### Analysis of outcome measures

300 neuromuscular patients and if applicable their partners will be included in the study. The primary analysis will be an intention-to-treat analysis on the area under the curve of the quality of life scores (average response during 6 months). A linear mixed model will be used with random factor group and fixed factors treatment, baseline score and type of neuromuscular disease. Other outcome parameters will be evaluated in a similar way and additional per protocol analyses will be carried out.

For the analyses SPSS version 17 statistical software will be used. A p-value of 0.05 will be considered statistically significant. Missing data will be imputed using multiple imputation techniques.

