#### Economic evaluation

An incremental cost-effectiveness analysis will be conducted from a societal perspective, relating differences in costs to difference in health outcome as measured by the Euroqol-5D, an instrument to evaluate different health states. Bootstrapping will be used for pair-wise comparisons in direct health care costs, direct non-health care costs, total direct costs, total indirect costs, and total costs between the two groups. Confidence intervals will be obtained by conventional re-sampling methods (bootstrapping). The cost effectiveness analysis will provide information on the marginal costs and effects of shared medical appointments relative to conventional one-to-one outpatient visits through the calculation of an incremental cost effectiveness ratio. Ratios will include the primary outcome of the trial, i.e., quality of life and two secondary outcome parameters; functional activities, and self-efficacy. Cost acceptability curves will be calculated showing the probability that the shared medical appointment is cost effective at specified ceiling ratios. In situations where there is no significant difference in effects, the use of cost-minimization analysis will be used for the reporting of cost differences only. Sensitivity analyses will be conducted, exploring the sensitivity of the conclusions to various sources of uncertainty, including sampling variation (e.g., differences in self-efficacy and functional abilities in both groups) and point-estimates (e.g., unit cost prices of major cost drivers).

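### The economic evaluation switches to cost-minimization when effects do not differ significantly, so a non-significant result is handled as equivalence without a margin or test

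*Protocol article*

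**What the plan says.** The Economic evaluation section under Statistical analysis plans an incremental cost-effectiveness analysis from a societal perspective, with the EQ-5D as the measure of health outcome. It names incremental ratios for quality of life, functional activities and self-efficacy, and bootstrapped confidence intervals. It then promises: "Cost acceptability curves will be calculated showing the probability that the shared medical appointment is cost effective at specified ceiling ratios".

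The next sentence is the rule at issue: "In situations where there is no significant difference in effects, the use of cost-minimization analysis will be used". It ends by limiting the report to cost differences.

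That section sets no significance level of its own. The preceding section, Analysis of outcome measures, does: "A p-value of 0.05 will be considered statistically significant".

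The Sample size section is built on superiority for a different instrument. It expects a "clinically relevant improvement in quality of life of 5 points on the total SF-36 score", and continues "Assuming a standard deviation of 12" and "92 patients need to be enrolled in both groups to achieve a statistical power of 80% (alpha = 0.05, two-sided". The number is then raised for non-evaluable patients, imbalance and subgroup analyses: "135 patients will be enrolled in both groups". No SD or target difference is given for the EQ-5D, and no equivalence or non-inferiority margin for any outcome.

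**The concern.** Cost-minimization is a valid form of analysis when the two options are known to have the same effect. Here the condition for using it is a failure to reject the null hypothesis in a superiority test. That result fits equal effects, but it also fits a real gain or a real loss that the trial could not detect. Without a margin and a test against it, the rule cannot tell these cases apart.

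Cost-effectiveness is in the title, in the design statement and among the strengths claimed in the Discussion, so the economic answer is a headline result. Neurologist time favours the group visit by design: 90 to 120 minutes shared by 6 to 10 patients is 90/10 = 9 to 120/6 = 20 minutes per patient, against 30 minutes for an individual visit. The group mentor adds cost back, and total societal cost is unknown. If the group visit does prove cheaper, setting the effect aside would endorse it without having excluded a loss in quality of life. If it proves dearer, a worthwhile gain could be set aside in the same way.

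**Working it through.** **Inputs.** From Sample size: difference 5 SF-36 points, SD 12, two-sided alpha 0.05, power 80%, 92 per arm required, 135 per arm planned. From Analysis of outcome measures: threshold p = 0.05. Clustering within group visits and the gain from baseline adjustment are ignored, because the protocol gives no figures for them.

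**The protocol's own figure.** The normal approximation is n = 2 × SD² × (1.96 + 0.842)² / difference² = 2 × 144 × 7.85 / 25 = 90.4, so 91 per arm. The two-sample t-test gives 91.4, rounded up to 92. The stated sample size reproduces and is not in question.

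**Precision at 135 per arm.** SE = 12 × √(2/135) = 1.46 points. The 95% half-width is 1.96 × 1.46 = 2.86 points. Any observed difference smaller than about 2.9 points is non-significant and triggers the rule. At 92 per arm the SE is 1.77 and the limit about 3.5 points.

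**What a non-significant result can contain.** An observed 2.5 points gives 2.5 ± 2.86, a 95% CI of about -0.4 to 5.4. It is non-significant, yet it includes the 5 points the protocol calls clinically relevant. By symmetry, -2.5 points gives about -5.4 to 0.4, which does not exclude a 5-point loss. At 135 per arm this applies to observed differences between 5 - 2.86 = 2.14 and 2.86 points in either direction. Smaller observed differences do exclude 5 points, but none excludes effects in both directions closer to zero than 2.86.

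**How often the rule triggers when a difference exists.** P(trigger) = 1 - [Φ(d/SE - 1.96) + Φ(-d/SE - 1.96)].

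| True SF-36 difference | 135 per arm | 92 per arm |
|---|---|---|
| 5 | 7% | 19% |
| 4 | 22% | 38% |
| 3 | 46% | 60% |
| 2.5 | 60% | 71% |
| 2 | 72% | 80% |

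For example, at 3 points and 135 per arm, 3/1.46 = 2.05, Φ(2.05 - 1.96) is about 0.54 and the other tail is negligible, so the rule triggers in about 46% of trials.

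**EQ-5D, illustration only.** The protocol gives no SD. If the SD of mean utility is assumed to be 0.15 to 0.30, the limit at 135 per arm is 1.96 × SD × √(2/135) = 0.036 to 0.072 utility. Over half a year that is 0.018 to 0.036 QALY. An assumed true difference of 0.05 utility would be non-significant in 22% to 72% of trials.

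**Fit with the rest of the section.** An acceptability curve needs the joint distribution of costs and effects. A report of cost differences only does not use it. The text does not say whether the curves are still produced once the rule applies.

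**The case against.** The strongest reply is that the rule does limited harm. At the 5-point difference for which the trial is designed, it triggers in only about 7% of trials at 135 per arm. The mixed-model analysis of quality of life is planned separately and reported regardless, so readers will see the effect estimates and their uncertainty. The economic section also plans sensitivity analyses that cover sampling variation in self-efficacy and functional abilities. The bootstrap is planned in any case, so no information is lost for good.

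Most of this stands. It limits the consequence to the economic summary and rules out three stronger readings that a reader might infer:

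- That the rule removes all uncertainty about effects. It does not, for the reasons just given.
- That a non-significant EQ-5D result is the likely outcome even if a worthwhile effect exists. The protocol gives no EQ-5D SD or worthwhile difference, and the answer moves from unlikely to likely with the values assumed.
- That the rule flatly contradicts the acceptability curves. Dropping the ratio and curves is the natural reading, but the curves are promised without condition, and the sentence could describe an added form of reporting.

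What the reply does not meet is the rule itself. A 7% rate at one assumed effect does not make non-significance evidence of equivalence, and the rate rises quickly for smaller true differences.

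**Conclusion.** The rule is wrong as written: it lets a non-significant superiority test decide that effects may be left out of the economic comparison. On the protocol's SD and sample size, this would happen in about 7%, 46% and 60% of trials at true SF-36 differences of 5, 3 and 2.5 points. Some of the results so handled would have confidence intervals that include the protocol's own relevant difference.

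These figures assume that the SF-36 is the trigger, that 135 per arm are evaluable, and that there is no clustering or baseline adjustment. Positive correlation within groups of 6 to 10 patients would raise them, and baseline adjustment would lower them. The trigger is itself undefined: the section names quality of life, functional activities and self-efficacy as effects, and quality of life has three instruments. A wrong economic conclusion is possible, not certain. The point should be corrected, but it does not touch data collection or the primary quality-of-life analysis.

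**What to change.** Delete the cost-minimization sentence. State instead that the joint bootstrap distribution of costs and EQ-5D effects will be reported whatever the p-value for effects, as a cost-effectiveness plane, an acceptability curve and incremental net benefit with a 95% CI, and that cost differences will be shown alongside. This also settles which effect measure governs the main economic result and whether the curves are kept.

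The cost is one sentence of wording. The bootstrap and the curves are already planned, and no new data are needed. The downside is that the trial can no longer report simply that one form of care is cheaper; it has to show how sure it is about costs and effects together.

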## Discussion

To the best of our knowledge, this study will be the first randomized controlled trial which evaluates the effect of shared medical appointments versus usual care for neuromuscular patients. Evidence shows that shared medical appointments can have substantial added value, deriving not only from sharing a health care professional's time, but also from sharing mutual experiences, particularly for patients with a chronic disease [2,3,40]. In the literature, group visits have been shown to result in fewer hospitalizations and emergency visits, increased patient satisfaction and increased self-efficacy as compared to usual one-to-one outpatient visits in elderly, chronically ill patients (Scott et al. 2004). In patients with diabetes, a randomized controlled trial demonstrated an increased frequency of preventive procedures among patients attending group visits, resulting in a better general health status as measured by the SF-36 [3]. Sadur et al (1999) demonstrated greater satisfaction with diabetes care, greater self-efficacy, better glycemic control, and lower service utilization among patients with diabetes who were randomly allocated to group visits as compared to counterparts who were allocated to usual care.

This study has several strengths. Firstly, shared medical appointments will be compared with usual care in a randomized design. This will enable to determine if there is additional value of shared medical appointments to the current management spectrum. Secondly, this study involves measuring effect of a treatment on partners of patients with a neuromuscular disease. Studies from Baanders et al (2007) and Timman (2010) show that living with a chronically ill person, specifically with a neuromuscular disorder, has an impact on the partner's life that goes beyond the consequences of care giving, for example consequences on personal life strain, social relations, financial burden, and intrinsic rewards [35]. And that marital satisfaction is a strong predictor of better wellbeing, both for patients and, even more so, for partners [31]. Thirdly, this study aims to determine the cost effectiveness of shared medical appointments as compared to care as usual. In current healthcare time is a scarce good. Efficiency goals are on top of every healthcare managers' list. When introducing a new way of delivering care, such as shared medical appointments, this preferably is just as or even more efficient than care as usual. Therefore it is important to take cost effectiveness of the intervention into account in this study. A limitation of this study can be the fact that it is a single center study. This may influence the transferability of the research results to other hospitals. Due to pragmatic and financial reasons the follow up time is limited to 6 months. For patients with neuromuscular disorders annual control visits are offered, this limits the number of shared medical appointments a patient receives during the study to one. Possibly the effect of group visits increase when attended several times. With this study design it is not possible to show this effect. A reflection of practice in this study, that could be a possible limitation, is inclusion of different patient groups. Although patients all have a chronic neuromuscular disease, possible differences in effects between patient groups could be difficult to show with this study design.

In conclusion, this study will provide greater insight in the (cost) effectiveness of shared medical appointments for neuromuscular patients. The concept of group visits or shared medical appointments is a typical example of organizing the delivery of health care in a different way, in an attempt to improve patient outcome within the limits of available resources. Many attempts at increasing efficiency of health care consist of reducing the amount of time health care professionals spend on specific activities. Such attempts risk, however, to jeopardize the quality of care [41]. When our study shows that group visits produce the alleged benefits, this may help to increase the acceptance of this innovative and creative way of using one of the most precious resources in health care more efficiently: time.

## List of abbreviations used

CPEO:Chronic progressive external ophthalmoplegia; CRAMP database: Computer Registry of All Myopathies and Polyneuropathies; FSHD: Facioscapulohumeral Muscular Dystrophy; IBM: Inclusion body myositis; INQOL: Individualized Neuromuscular Quality of Life; OPMD: Oculopharyngeal Muscular Dystrophy; SMA: shared medical appointment; RCT: randomized controlled trial; RUNMC: Radboud University Nijmegen Medical Center

## Appendix 1

Process of a shared medical appointment:

- Patient registers at the outpatient clinic an led to the group visit room by the group mentor

- Patients are being asked to fill out a privacy form

- Group mentor starts with a brief introduction, in which the process of an SMA and privacy aspects are explained

- Neurologist starts with consulting the first patient

- Individual medical needs and questions of the patient are being discussed with the neurologist

- The neurologist gives information to the patient and his/her partner

- If applicable, the group mentor asks if fellow patients have experiences on this subject they want to share or questions they want to ask to fellow patients or the neurologist

- Neurologist finishes consultation with the first patient and writes notes in the patient record

- The neurologist lifts the second patient record and starts with consulting the second patient, and so on till all patients have had their consultation

- The group mentor asks if all questions are answered and if so closes the group visit

- If applicable, physical examination of a patient is being executed by the neurologist in a separate room, any necessary receipts or blood samples are being taken care of as well

- Group mentor and neurologist leave the group visit room and fill out patient records and patient letters
